### Interventions

The interventions consist of 2 mobile apps designed to improve physical activity. The first is SCIPP: the Self-Control Intervention App, which was specifically designed for this study, and the second is Google Fit, a mobile lifestyle intervention aimed at increasing physical activity.

#### SCIPP: the Self-Control Intervention App

SCIPP is a mobile app based on the pen-and-paper format of SCT [24-26]. SCIPP is available on Android and provides users with a new daily challenge for 14 days. This daily challenge asks users to perform an everyday activity—such as opening the door or turning on the light—with their nondominant hand. After accepting the challenge, users are reminded of the daily challenge 4 times a day. After 14 days, the app notifies the user that the training has concluded. By restarting the app, the intervention can be used for a longer period—in the case of this study, up to 28 days.

We have previously established the feasibility and preliminary effectiveness of mobile SCT in young adults [32]. This study showed that self-control did improve in participants who used an SCT app, whereas self-control did not increase in participants who received SCT via email and participants in a control group that did not receive SCT. The app was then redesigned with and for people with SMI to meet their cognitive capabilities and preferences following a participatory design study [50]. It meets the following requirements for suitable SCT from the patients’ perspective: (1) behavior change is framed as a shared, unpredictable process; (2) visual rewards and explanations are given; (3) the app uses reduced textual and numerical information; and (4) the app provides accessible means for feedback and personal goals. In addition, the app sends reminders throughout the day to remind users of the daily challenge. This was considered specifically important as reminders appeared to be the main advantage of an app over email in the previous study [32]. Participants in the app condition of the previous study appreciated the reminders and even requested more, whereas participants in the email condition indicated that they often forgot about tasks and would have liked to have reminders. Finally, the SCT app also incorporates several other persuasive features to promote engagement and adherence [30,51,52], including reduction, self-monitoring, social role, praise, personalization, real-world feel, and liking. Reduction and self-monitoring features reduce complex behavior in simpler, smaller tasks and allow users to track their performance on these tasks. In the SCT app, this means that users monitor daily self-control challenges (Figures 1-2). Social role and praise enable users to form a social relationship with the app, which provides praise when the target behavior is performed. In the SCT app, this is embedded in the virtual coach Scipp (Figure 3). Personalization and real-world feel were incorporated through tangible, personalized goals and feedback (Figure 4), whereas liking refers to the look and feel of the app and is incorporated into the overall minimalist, colorful esthetic used.

**Figure 1 figure1:**
[figure not shown]
Screenshot of daily challenges with reminders in SCIPP: the Self-Control Intervention App. Daily challenges are easily found on the main page and explained visually. Users receive 4 daily reminders of the daily challenge.

**Figure 2 figure2:**
[figure not shown]
Screenshot of the process page with a winding mountain path in SCIPP: the Self-Control Intervention App. Users self-monitor daily challenges. As behavior change is an unpredictable process, the mountain visualization includes ups and downs, and participants can also report when they were not able to do a challenge.

**Figure 3 figure3:**
[figure not shown]
Screenshot of virtual coach Scipp in SCIPP: the Self-Control Intervention App. Virtual coach Scipp praises users for completing challenges. She also frames behavior change as a shared process and invites users to celebrate success with their broader social network after certain milestones, such as the first successful day of self-control training.

**Figure 4 figure4:**
[figure not shown]
Screenshot of providing feedback on challenge difficulty in SCIPP: the Self-Control Intervention App. Users can set their own motivation for training self-control and provide feedback on the difficulty of the challenges. Once training is completed, this initial goal is shown to the users and can be adapted if needed.

#### Google Fit

Google Fit is a freely available mobile health tracking platform developed by Google in collaboration with the World Health Organization and the American Heart Association. Google Fit can be considered a goal-directed, cognitive intervention that incorporates various behavior change techniques to motivate the user to be more active. These include the ability to set a personal activity and step count goal, self-monitor activities in a personal dairy, and receive customized feedback based on health and activity history. To monitor physical fitness activities, Google Fit uses sensors from the user’s mobile device or external activity trackers. It translates each minute of moderately intense activity into a Heart Point, and more intense activities result in more points. In addition, the number of steps is tracked. It is available on the Android and iOS operating systems, but in this study, only the Android version will be used.

Google Fit was selected as the physical activity intervention in this study in line with the rationale provided in the Introduction section—it does not require additional support from staff; it is based on reflective processes of self-control (ie, a focus on cognitive processes such as goal setting) and, thus, can be complemented with the novel SCT intervention; and it is likely suitable for the cognitive abilities of people with SMI. The latter was determined based on the assessment of the Regional Public Health Services of the Netherlands, which assessed Google Fit as reliable, theory-informed, secure, and user-friendly, including short, concrete text free of difficult jargon or medical terms [53]. Although no evidence is available regarding the effectiveness of Google Fit in increasing the physical activity of people with SMI, it has been successfully used in people with poor mental health [54].

### Material and Measures

#### Overview

The primary study parameters are daily physical activity and self-control. Daily physical activity will be measured using a wearable accelerometer, the ActiGraph GTX+ [55,56]. Daily self-control will be measured via experience sampling.

#### Physical Activity

The ActiGraph GT3X+ and ActiLife software (version 6.8.0; ActiGraph) will be used to measure and analyze physical activity. The accelerometer is worn on the right hip and held in place with an elastic strap between 2 belt loops. Patients without belt loops will use a pouch pinned at the same location. The ActiGraph GT3X+ has a high inter- and intra-instrumental reliability [57] and validity [56]. It has been used successfully in previous studies with people with SMI to examine physical activity and sedentary behavior [6,58,59]. None of these studies reported usability, safety, or other issues related to the use of the ActiGraph GT3X+ in this population, which makes it a reliable, valid, and appropriate choice for measuring physical activity in this study.

Physical activity is operationalized as the daily average of total activity counts per hour, which is a continuous and detailed outcome variable of physical activity [6]. More counts indicate a higher level of physical activity. Following existing procedures for valid measurement of physical activity using the ActiGraph GT3X+ in this population, a wear time of >6 hours per day for at least 3 days will be used as the criterion for sufficient measurement [6,58].

#### Daily Self-control

To distribute questionnaires, the mobile survey distribution platform Ethica Data [60] will be used. Ethica is a web-based platform that is designed for researchers to create, modify, and distribute momentary surveys for experience sampling research. It allows researchers to obtain and view the data of the participant in real time to identify possible errors while the study is still running. Furthermore, it amplifies the ecological validity, possibilities, and reliability of frequent data collection [61]. Participants use their smartphones to complete the surveys. This reduces strain on participants as they do not have to carry with them additional study-related materials. Finally, trigger logistics help reduce participant burden by sending automatic reminders to fill out surveys [62].

Daily self-control will be measured using 2 items from the State Self-Control Scale [63] and 2 items specifically developed for this study. Participants use a 5-point slider ranging from 1 (*not at all*) to 5 (*very much*) to reflect on recent self-control experiences. All questions start with “In the past couple of hours...” Participants answer questions about decision-making (“it’s hard to make up my mind about even simple things”), subjective feelings of ego depletion (“I had less mental and emotional energy than I normally have”), goal-directed behavior (“I was able to do what I had planned”), and inhibitory control (“I was able to resist temptations”). We have previously used this questionnaire to measure daily self-control in students [64] and rephrased the items for people with SMI to improve clarity and brevity. A small pilot study with 5 patients receiving outpatient psychotherapeutic care showed that the rephrased items had high face validity, feasibility, and comprehension [65].

#### Trait Self-control and Cognitive Control

Generalization measures assess the intervention effect on untrained tasks and are important to establish the external validity in SCEDs [36]. The SCRIBE guidelines [37] recommend that generalization measures are taken repeatedly, although not as frequently as the main outcome measures. In this study, trait self-control and cognitive control are used as generalization measures and assessed every 5 days (at least once per phase). This combination of measures is used as self-control is a multifaceted construct and it is recommended to use more than one type of measurement instrument to assess it [66].

Trait self-control is measured using the Brief Self-Control Scale (BSCS). The BSCS is a validated, brief, and psychometrically sound measure of individual differences in self-control that consists of 13 items [19,66,67]. The BSCS measures several aspects of trait self-control, including inhibitory and initiatory control [68]. Participants rate the extent to which a statement, for example, “I am good at resisting temptation,” matches them on a 5-point Likert scale ranging from 1 (*not at all*) to 5 (*very much*). A total score for self-control will be created by taking the sum of all items after recoding negatively phrased items (Cronbach α=.83-.85 [69]). Higher scores indicate higher levels of self-control, which has a medium effect on behavioral outcomes, showing criterion validity [70].

Cognitive control will be measured using the go/no-go task. This is a well-studied measure of cognitive control and has been used in previous research to assess self-control [32]. In the go/no-go task, participants are instructed to respond to target stimuli but must refrain from responding to nontarget stimuli, which requires suppressing a behavioral response. In this study, we will use average reaction time as the main parameter of cognitive control, with shorter reaction times reflecting more self-control [32,71].

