This requires interventions that patients can work on independently; that do not require a high level of cognitive skills; and that target the intention-behavior gap that is common in interventions that are based on cognitive, reflective models. A promising focal point of these interventions is self-control—the ability to prevent or override unwanted thoughts or behaviors in favor of higher-order goals [19]. Studies have shown that self-control plays an important role in a broad range of goal-directed behaviors, including academic achievement, aggression regulation, and healthy eating and physical activity [19]. According to Friese et al [20], the role of self-control can be explained through three interacting components: (1) reflective processes such as personal goals, (2) impulsive processes such as automatic approach and avoidance tendencies, and (3) self-control abilities that allow for the control of impulsive processes and transfer of reflective processes into behavior. Owing to the large body of evidence that shows the relationship between self-control and health behaviors, self-control is an important element of many existing interventions. Even so, these mostly focus on self-control as a reflective process and teach reflective strategies such as goal setting, mental contrasting, and mental transformations [21], whereas interventions that address impulsive processes are underrepresented.

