#### Piecewise Linear Regression Analysis

To supplement the visual analysis, we will conduct piecewise linear regression analyses (PLMs) using the *scan* package [77]. PLM is an approach to analyzing time-series data that are segmented into phases, including SCEDs [77,78]. The PLM model calculates 4 parameters (intercept, trend, level, and slope) separately for data from each phase, allowing for a comparison between phases. In this case, *intercept* refers to the performance at the start of the study, *trend* effects refer to the continuous increase in the behavior over time, *level* effects refer to the constant and instant effect of the intervention, and *slope* effects refer to the change in continuous increase initiated by the intervention.

Using the PLM, we will construct a linear model for each individual patient, including a *P* value, *R*^2^ effect size, and beta weights for trend, level, and slope effects. We will use a cutoff of *P*<.05 to determine significant effects.

In SCED I only, we will also construct a multilevel PLM to aggregate single-case findings across all participants included. Aggregation improves the external validity of the findings by providing overall trend, level, and slope effects and allows for the exploration and quantification of moderation effects using random slopes [77]. First, we will include random slopes in the multilevel PLM to examine whether trend, level, and slope effects differ significantly between participants. If this is the case, we will subsequently consider the interactions between body weight, height, stage of change, clinic type, intervention use, trait self-control, and cognitive control as potential moderators of the effect. As there are no existing hypotheses about moderation, we will not use confirmatory *P* values in this analysis but merely report any findings as preliminary and exploratory.

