#### Reliable Change in Generalization Measures

We will explore individual changes in generalization measures of trait self-control and cognitive control by comparing the means of pre- and postintervention scores obtained during baseline, end of intervention phase C, and follow-up.

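### Go/no-go cognitive control is read from average reaction time alone, so faster responding with better control cannot be told apart from faster responding with less inhibition

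*Protocol article*

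**What the plan says.** The Protocol article (Trait Self-control and Cognitive Control) states that "Cognitive control will be measured using the go/no-go task". It describes the task as one in which participants respond to targets but "must refrain from responding to nontarget stimuli, which requires suppressing a behavioral response". It then fixes the parameter and its direction: "we will use average reaction time as the main parameter of cognitive control, with shorter reaction times reflecting more self-control". Two sources are cited for this, one of them the earlier study of a mobile self-control training (SCT) app. The article names no error rate, sensitivity index or accuracy condition for the task.

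The measure is repeated every 5 days and at least once per phase. It is used in two places:

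- Under Reliable Change in Generalization Measures, individual change is explored by "comparing the means of pre- and postintervention scores obtained during baseline, end of intervention phase C, and follow-up".
- Under Piecewise Linear Regression Analysis, for SCED I only, the multilevel model may consider "trait self-control, and cognitive control as potential moderators of the effect". This happens only if effects differ between participants, and the results are to be reported as preliminary.

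**The concern.** The introduction defines self-control as "the ability to prevent or override unwanted thoughts or behaviors in favor of higher-order goals", and the task description is in the same spirit: what is tested is withholding a response. In a go/no-go task, withholding succeeds or fails on the nontarget trials. A successful inhibition yields no reaction time, and a failed one is a commission error. The main score thus leaves out the behaviour that the paragraph says the task demands.

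Reaction time also depends on how cautious the participant is. Someone who becomes less careful responds sooner and fails to withhold more often. Someone who learns to pause responds later and fails less often. With no accuracy condition, the first change is read as more self-control and the second as less.

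This matters because the go/no-go task is the only performance-based measure of self-control in the study. Daily self-control and the Brief Self-Control Scale are self-reports by participants who know which phase they are in. The pre/post comparison is made person by person, so one participant's change of response strategy is not averaged out.

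**Working it through.** The article gives no figure for this measure, so there is nothing to reproduce. The check asks whether a shorter time identifies the direction of change in control. All parameters below are assumptions.

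**Closed-form check.** Take a two-boundary diffusion model with unbiased start, unit noise, drift v (efficiency) and boundary separation a (caution):

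- error rate = 1 / (1 + exp(v·a))
- mean decision time = (a / 2v) · tanh(v·a / 2)

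| Setting | Error rate | Decision time |
|---|---|---|
| v = 2, a = 1.5 | 1/(1+e^3.0) = 4.7% | 0.375 × tanh(1.5) = 339 ms |
| v = 2, a = 1.0 | 1/(1+e^2.0) = 11.9% | 0.25 × tanh(1.0) = 190 ms |
| v = 2, a = 0.8 | 1/(1+e^1.6) = 16.8% | 0.20 × tanh(0.8) = 133 ms |
| v = 3, a = 1.0 | 1/(1+e^3.0) = 4.7% | 0.167 × tanh(1.5) = 151 ms |

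- *Caution falls, ability unchanged* (row 1 to row 2): time shortens by 339 − 190 = 149 ms and errors rise from 4.7% to 11.9%.
- *Ability rises, caution unchanged* (row 2 to row 4): time shortens by 190 − 151 = 39 ms and errors fall from 11.9% to 4.7%.

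The plan's rule scores both changes as more self-control. Only the errors separate them.

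This model is a symmetric two-choice model. Its error rate applies equally to missed targets, so reading it as the commission rate is a further assumption. A simulation laid out as a go/no-go task avoids that.

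**Go/no-go simulation.** Settings: 20,000 trials, 75% go trials, go drift 3.0, non-decision time 250 ms, 1 s response window. Only the response threshold was lowered, from 1.0 to 0.4.

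| No-go drift | Mean go reaction time | Commission errors | Go omissions |
|---|---|---|---|
| −1.0 | 581 to 371 ms | 9.1% to 30.0% | 1.1% to 7.2% |
| −1.5 | 586 to 372 ms | 3.7% to 22.0% | 1.2% to 7.1% |
| −2.5 | 581 to 371 ms | 0.5% to 11.1% | 1.2% to 7.4% |

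The direction is the same at every no-go drift tried. Averaging over all responses instead of go responses hardly matters (at drift −1.5, 588 to 375 ms against 586 to 372 ms). The ambiguity does not come from which trials are averaged.

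**Would an error index alone do better?** In the closed-form model, raise caution from 1.0 to 1.5 at v = 2. Errors fall from 11.9% to 4.7%. With equal error rates e on both trial types, d-prime = 2·Φ⁻¹(1 − e), which rises from 2 × 1.18 = 2.4 to 2 × 1.67 = 3.3. A participant who is merely more cautious would then count as improved. No single index tried here resolves the question, but the pair of time and errors does.

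**The case against.** - **The scoring is sourced.** It follows two cited studies, one of them the earlier SCT app study, and comparability is a legitimate aim. Those sources could not be seen, so whether they support this reading is open. This is a good reason to keep reaction time. It does not supply the missing accuracy condition.
- **A main parameter need not be the only one.** Secondary indices and the handling of error trials may stand in a fuller document. That stands, and a reader should not infer that errors will go unrecorded or unreported. The fair target is what the article fixes: the leading parameter and a direction without a condition.
- **Faster can mean better.** This also stands, as the higher-drift row shows. A reader might infer that the rule has the wrong sign, or that participants will be credited for becoming impulsive. The documents support neither: nothing in them suggests that caution, rather than efficiency, will change.
- **The impact is small.** Agreed. The measure is exploratory, it does not set the SCED II phase length, and no test or decision rule is attached to its change. As a moderator, the direction label leaves the fitted interaction unchanged and affects only how it is described.
- **Recruitment has begun.** Under Results, 6 participants had been included by March 2023. Replacing the main parameter now could look like a switch after data were collected; adding an accompanying measure is less open to that criticism.

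**Conclusion.** The point holds as one of incomplete scoring. As written, the article's rule cannot distinguish faster responding with no more errors from faster responding with more failures to withhold, although withholding is what the task is said to demand. A generalization gain, or a statement that people with better cognitive control respond differently to SCT, could therefore be misread. The primary outcome (activity counts) and the secondary outcome (daily self-control) are untouched.

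The size cannot be given for this trial. Under the assumed models, a shift in caution alone can shorten reaction time by about 200 ms while commission errors rise by roughly 11 to 21 percentage points (0.5% to 11.1%, up to 9.1% to 30.0%). These figures show what the rule would miss if such a shift occurred; they do not show that it will occur.

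It might be tempting to conclude that commission errors or d-prime should replace reaction time. That does not follow, since either one alone credits a participant who has only become more cautious.

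**What to change.** Keep mean reaction time, taken over correct go trials, for comparability with the earlier app study, after checking that this study averaged in the same way. At every assessment, report beside it the no-go commission-error rate and the go omission rate. State the reading in advance of the analysis:

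- A shorter time counts as more self-control only when commission errors do not rise.
- Fewer commission errors count as better only when neither reaction time nor omissions rise.
- Any other combination is reported as inconclusive.

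Apply the same joint reading where cognitive control is considered as a moderator, and mark the change as added after recruitment began.

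The cost is a few sentences and slightly more analysis. No new measurement is needed, assuming responses are stored trial by trial. The real price is that some individual changes will be reported as inconclusive.
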